**Fig. 2 Fig2:**
[figure not shown]
Research design for the different groups and interventions of e-Vita COPD

Organisational and technical differences are depicted in Fig. 2: three different care groups and two different web portals are included. Two different methods of implementation are distinguished within group 1 and 2: one with high level of personal assistance and one with low level of personal assistance. All patients in group 1 and 2 start with a personal instruction by the primary care nurse during a regular control visit. Patients will be randomly subdivided in two groups by computer by research assistants (randomisation is computerised to prevent human influence) with high (a) and low (b) level of support. In group 1a, high level support implies home visits for patients by a research nurse who accompanies the use of the web portal. In group 2a, high level support implies telephone consultation for patients by a research nurse who accompanies use of the web portal. In group 1b and 2b low level support implies that the primary care nurse shows the patient only once how to use the web portal (the usual organisational implementation method in daily practice) without any follow-up instruction. In group 3 the web portal is offered as free use: patients will receive instructions from the web portal itself. There will be no active support from caregivers or research nurses.

The groups differ in organisation, area, use of the web portal, and integration of the portal in a COPD disease management program (Fig. 3); these characteristics are based on Dutch reports of care groups [28]:

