Because the most powerful studies are prospective studies, we chose a prospective parallel cohort design. We asked three primary care groups to invite their COPD patients for the e-Vita study. Because there are several differences between the groups (Fig. 3), we can not compare the COPD cohorts by combining data across three different groups. We chose for an interrupted time series (ITS) design to evaluate clinical outcomes (CCQ) within each group. In ITS studies, data are collected at multiple time points before and after an intervention in order to detect whether or not the intervention has a significantly greater effect than any underlying secular trend [26]. ITS can detect changes that are delayed or intermittent. It can also determine if the change is permanent or temporary. In addition, it allows evaluation of variables which are changing before the intervention, for instance, by comparing slopes of trend lines before and after the intervention. Finally, ITS makes it easier to control for confounding variables and regression to the mean [27]. The ITS will be performed according to guidelines of the EPOC Cochrane group [25]. Although well-conducted randomised trials provide the most reliable evidence on the effectiveness of interventions, they are not feasible for our setting of an implementation design with organisational changes in a real-life health care system within three different care groups with different demands. An advantage of an ITS design is that it allows for the statistical investigation of potential biases in the estimate of the effect of the intervention.

In addition to clinical outcomes, we also want to investigate the effect of different organisational implementation methods. Therefore we will implement the platform in group 1 and 2 using different methods. Differences will be measured using a parallel cohort design. To be certain that intervention groups will be balanced in known and unknown prognostic factors in the long run we will use randomisation within group 1 and 2. To rule out human influences we will randomise online for the level of support.

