**Fig. 3 Fig3:**
[figure not shown]
The different characteristics of group 1, 2, and 3

Group 1 will start with COPD disease management simultaneous to implementation of the web portal. The web portal is integrated in the disease management program (integrated use).Group 2 is used to working with a COPD disease management program. They will start with the web portal, which is integrated in their own disease management program (integrated use).Group 3 is used to working with a COPD disease management program. They will start with the web portal, but the web portal is not integrated in their own disease management program (free use).

As was described above, the implementation of the portal will be studied using a prospective parallel cohort design. The clinical effects of the web portal will be investigated using an interrupted times series (ITS) study design (Fig. 4) and measured according to changes in health status with the Clinical COPD Questionnaire (CCQ, see Appendix 1). ITS design includes multiple observations over time that are ‘interrupted’ by interventions. The time intervals between the observations T1, T2, T3, and T4 are 6 months, to detect the change in CCQ in a trend and slope over the total period of time. The time intervals between the 3 measurements of each observation T1, T2, T3, and T4 is two weeks, based on the high responsiveness of CCQ [29]. The ITS will be performed according to guidelines of the EPOC Cochrane group [30]. The aim of an ITS design is to detect confounding trends by performing several measurements at specified time intervals, before and after the intervention. An advantage of an ITS design is that it allows for the statistical investigation of potential biases in the estimate of the effect of the intervention.

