Next, we will offer patients an online interactive care platform or web portal. The portal provides disease specific education and tips that fit their personal disease management program. In addition, the portal provides tools to report and monitor personal health goals, actions and health-related quality of life that can be shared with the patients’ own practice nurses. The portal in group 1 and 2 has better quality and more advanced possibilities for monitoring health goals with actions than the portal in group 3. The portal will be provided for a period of 15 months. Patients are informed by letter about the web portal. Patients in group 3 who agree to use the portal will receive instructions and log in information by e-mail. Patients in group 1 and 2 who agree to use the portal will be invited by their own practice nurses for intake. During intake the practice nurse defines a personal health goal together with the patient and gives instructions how and why to use the portal. Participants continue to receive regular COPD care by their GP and nurse practitioner according to the disease management program of the care group. Stable COPD patients visit their nurse practitioner yearly to check up on their disease management. The patient portal can be used by care professionals to prepare consultation or to monitor patients in-between their visits to their general practice.

Third, a subgroup of participants (1a and 2a) will receive extra support to use the portal by home visits or with instructions by telephone. During the home visit and consultation it will be checked if patients are able to log on the portal, if they understand the possibilities of the portal, and if they have started working on their personal health goal using the portal.

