### Data analysis

Along with our research design, analyses will be multilevel:To investigate the effect of the use of the web portal on the primary clinical outcomes, the ITS data will be analysed. The preferred method to analyse ITS studies is a statistical comparison of time trends before and after the intervention. Time series analysis using ARIMA models is one way of analysing the data, but there are a number of statistical techniques that can be used depending on the characteristics of the data, the number of data points available and whether autocorrelation is present. The final choice for the method to analyse the data will be made when the total set of data is available after consultation of a statistician.To investigate the effects of organisational aspects uptake of the portal will be analysed for care group 1, 2 and 3 using Chi Square tests (Fishers’ Exact Test for categorical variables and *F*-tests for continuous variables) and (repeated measures) ANOVA analyses. To analyse the effects of organizational aspects as described in the paper, the groups will be compared.To investigate the effect of integration of the web portal in daily practice, outcomes within integrated (group 1 and 2) and the free use groups (group 3) will be analysed using Chi Square tests (Fishers’ Exact Test for categorical variables and *F*-tests for continuous variables) and (repeated measures) ANOVA analyses.To investigate the effect of different organisational implementation methods, outcomes within groups with high level support (1a and 2a) and low level support (1b, 2b and 3) will be analysed using Chi Square tests (Fishers’ Exact Test for categorical variables and *F*-tests for continuous variables) and (repeated measures) ANOVA analyses.To explore correlation between self efficacy, sociodemographic characteristics on the one hand and adoption of the portal and clinical outcomes on the other hand, Pearson product-moment coefficients will be calculated across all research groups.To make a cost-effectiveness analysis, the direct costs of the different organisational implementation methods will be defined and analysed parallel to the effects of the portal in terms of Quality of Life (EQ-5D).

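### The only named support-level contrast pools home visits (1a) with telephone consultation (2a) and has no term for care group, so alone it cannot show which implementation method worked

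*Protocol article*

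**What the plan says.** All places are in the protocol article.

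- **Methods/Design, text under Fig. 2.** "In group 1a, high level support implies home visits for patients by a research nurse who accompanies the use of the web portal". For the other care group, "In group 2a, high level support implies telephone consultation for patients by a research nurse who accompanies use of the web portal". Low support in 1b and 2b is a single demonstration by the primary care nurse. Group 3 gets no active support.
- **Methods/Design, on allocation.** For the level of support, "we will use randomisation within group 1 and 2". Group 3 is not randomised.
- **Text under Fig. 3.** The care groups differ in more than support: "Group 1 will start with COPD disease management simultaneous to implementation of the web portal", whereas group 2 already works with such a programme.
- **Intervention.** Both modes share the same checks: "During the home visit and consultation it will be checked if patients are able to log on the portal", and likewise whether they understand the portal and have started on their personal goal.
- **Data analysis.** For implementation methods, "outcomes within groups with high level support (1a and 2a) and low level support (1b, 2b and 3) will be analysed" with chi-square, Fisher's exact or F-tests and (repeated measures) ANOVA. No 1a vs 1b or 2a vs 2b contrast is named, nor stratification by care group, nor an interaction.
- **Methods/Design, aims.** A stated aim is to find the optimal organisational implementation method. The design is also said to control for confounding at the organisational level.

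**The concern.** Home visits occur only in care group 1 and telephone consultation only in care group 2. The named contrast merges them into one high-support arm and ignores the care group within which patients were randomised. A reader choosing an implementation method needs to know whether visits added something in a setting like group 1, and whether calls added something in a setting like group 2. One pooled figure answers neither question unless the two effects happen to be equal, and the article neither assumes nor tests that. If the effects differ, an effective mode can be diluted to the point of being missed, or an ineffective one can be credited with an effect.

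The randomisation already supplies the two comparisons that would answer these questions, but the analysis text does not use them separately.

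**Working it through.** **1. The contrast set against the design.**

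| Cell | Support | Care group | Randomised for support | Place in the contrast |
|---|---|---|---|---|
| 1a | home visits | 1 | yes | high |
| 2a | telephone | 2 | yes | high |
| 1b | one demonstration | 1 | yes | low |
| 2b | one demonstration | 2 | yes | low |
| 3 | none (free use) | 3 | no | low |

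Mode and care group coincide completely on the high side. With equal cells, the high side is one half group 1 and one half group 2, and the low side is one third each of groups 1, 2 and 3. The care-group mix therefore differs between the two sides, and the whole difference comes from adding group 3. Among 1a, 1b, 2a and 2b alone the mix is balanced.

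**2. The plan's own size (Power calculation).** Inputs: difference 0.5 CCQ points, SD 0.75, power 80%, alpha 0.05.
n per arm = 2 × (1.96 + 0.84)² × 0.75² / 0.5² ≈ 35.3, so 36. A two-sample t-test gives 36.3, so 37. The stated 37 reproduces as a two-sided, two-arm comparison.

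In the article the 0.5 is the expected effect of the portal (2.0 − 1.5). Arms 1a, 1b, 2a and 2b all receive the portal, so 0.5 is not a planned high-versus-low difference. Below it is used only as an assumed support effect.

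**3. Pooled effect for assumed mode effects.** With equal numbers in 1a and 2a, pooled = (home + telephone) / 2.

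| Home | Telephone | Pooled |
|---|---|---|
| 0.5 | 0.5 | 0.5 |
| 0.5 | 0.25 | 0.375 |
| 0.5 | 0 | 0.25 |

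The pooled figure matches both modes only in the first row.

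**4. Power, 37 evaluable per arm, SD 0.75, two-sided 0.05, normal approximation.** Power = Φ(effect / SE − 1.96).

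- One randomised contrast, 37 vs 37: SE = 0.75 × √(2/37) = 0.174. For 0.5, power = 82% (81% by t-test).
- Pooled randomised arms, 74 vs 74: SE = 0.75 × √(2/74) = 0.123. For 0.25, power = 53%. For 0.5 (equal mode effects), 98%.
- Pooled with group 3, 74 vs 111: SE = 0.75 × √(1/74 + 1/111) = 0.113. For 0.25, power = 60%, if group 3 behaves like 1b and 2b.
- Interaction (difference between the two support effects): SE = 0.75 × √(4/37) = 0.247. Power is 53% for a difference of 0.5 and 17% for 0.25.

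The article enrols 45 per arm. A 20% loss leaves 36 rather than 37, which lowers the single-contrast power by about one percentage point.

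**The case against.** The strongest reply is that the factor under study is the level of personal assistance, not its mode. The hypotheses speak of greater personal support, chiefly for portal use, and both modes carry the same checks. Averaging a support strategy adapted to each setting over two settings is a legitimate target. This stands. The pooled estimate is not meaningless; it is insufficient as the only named contrast when the aim is the optimal method.

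A second reply is that a journal article leaves component contrasts and stratification to the full plan. For unmentioned detail that would be right. Here the article itself specifies a contrast, and that contrast sets aside the care groups within which support was randomised.

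Four stronger readings are tempting and are not supported:

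- *The article itself forbids this pooling.* It does say "we can not compare the COPD cohorts by combining data across three different groups", but that sentence introduces the interrupted time series for clinical outcomes within each group. The implementation comparison follows as a separate matter. The reason given, differences between the groups, is relevant here, but it is not an explicit bar on this contrast.
- *The trial was sized to detect 0.5 points between support levels.* The 0.5 is the portal effect, as shown above.
- *Cost-effectiveness will rest on a blended cost.* Data analysis refers to the costs of the different implementation methods in the plural, and the Costs section names home visits and telephone interviews as separate items.
- *Confounding of mode with care group biases the high-versus-low comparison.* With equal cells it does not, among the randomised arms. It only prevents a 1a vs 2a difference from being read as an effect of mode.

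**Conclusion.** The point holds as a defect in the planned contrast, not in the design. The randomised comparisons 1a vs 1b and 2a vs 2b are intact. The contrast as written averages two modes, adds a non-randomised group to the low side and has no term for care group. Alone it cannot inform the choice of implementation method.

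The size depends on how far the two mode effects differ, on which the article gives no figure. If they are equal, pooling two modes does no harm and gains precision. At the assumed extreme of 0.5 and 0, the pooled effect is 0.25, with 53% to 60% power against 82% for the effective mode alone. These are illustrations on the CCQ. Data analysis says only that outcomes will be analysed, so portal use and satisfaction may matter more for this comparison. Likewise, about 80% power for each separate contrast holds only if added support itself shifts CCQ by 0.5 points on top of the portal.

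**What to change.** In Data analysis, replace the single support-level contrast with the following:

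1. Report two randomised contrasts separately: 1a vs 1b (home visits added to the usual implementation, group 1) and 2a vs 2b (telephone consultation added, group 2).
2. Give any combined high-versus-low estimate from 1a, 1b, 2a and 2b only, stratified by care group.
3. Report the support-by-care-group interaction with its confidence interval, as supportive.
4. State that a difference between 1a and 2a cannot be attributed to mode, because each mode exists in one care group only.

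No patients, visits or measurements are added. The cost is precision: the standard error of a separate contrast is 0.174 against 0.123 for the pooled randomised arms. The interaction test is weak (53% power even for a 0.5-point difference), so a non-significant result must not be read as evidence that the two modes work equally well. The revised text should not claim that the sample size was planned for a 0.5-point support effect.

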**Fig. 3 Fig3:**
[figure not shown]
The different characteristics of group 1, 2, and 3

Group 1 will start with COPD disease management simultaneous to implementation of the web portal. The web portal is integrated in the disease management program (integrated use).Group 2 is used to working with a COPD disease management program. They will start with the web portal, which is integrated in their own disease management program (integrated use).Group 3 is used to working with a COPD disease management program. They will start with the web portal, but the web portal is not integrated in their own disease management program (free use).

As was described above, the implementation of the portal will be studied using a prospective parallel cohort design. The clinical effects of the web portal will be investigated using an interrupted times series (ITS) study design (Fig. 4) and measured according to changes in health status with the Clinical COPD Questionnaire (CCQ, see Appendix 1). ITS design includes multiple observations over time that are ‘interrupted’ by interventions. The time intervals between the observations T1, T2, T3, and T4 are 6 months, to detect the change in CCQ in a trend and slope over the total period of time. The time intervals between the 3 measurements of each observation T1, T2, T3, and T4 is two weeks, based on the high responsiveness of CCQ [29]. The ITS will be performed according to guidelines of the EPOC Cochrane group [30]. The aim of an ITS design is to detect confounding trends by performing several measurements at specified time intervals, before and after the intervention. An advantage of an ITS design is that it allows for the statistical investigation of potential biases in the estimate of the effect of the intervention.

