**Fig. 5 Fig5:**
[figure not shown]
Interventions per group

In group 1 all caregivers (GPs as well as practice nurses) will be trained to provide COPD care according to an evidence based disease management program; subsequently they implement the COPD care program in their practices under supervision of a specialized nurse. Practice nurses will receive support by a research nurse to make sure their records of COPD patients are up-to-date and to prepare consultation with their patients according to the disease management program. In addition, all practice nurses will be trained to use the web portal and to communicate with patients according to the principles of self-management.In group 2 all caregivers (GPs as well as practice nurses) will be trained shortly to ameliorate their skills in COPD care according to an evidence based disease management program that they already use. All practice nurses will be trained to use the web portal and to communicate with patients according to the principles of self-management. The training is developed and provided for by the e-Vita study group and is based on national and international guidelines.In group 3 caregivers will not receive any training. Patients will receive a brochure how to use the web portal.

The type of intervention is adopted by the care groups after thorough consideration and discussion. The e-Vita study group determined the type of platform and the level of support.

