### Power calculation

Health status of patients with COPD generally decreases over time. Recent research on disease management programs in COPD in primary care shows that a general increase of 1.5 to 2.0 points (SD 0.75) in CCQ can be expected during a one year period [37]. In our study we offer patients a web portal in addition to their regular disease management program. We therefore expect that the regular deterioration in CCQ (from 1.5 to 2.0 points) will change to stabilisation of health status at 1.5 CCQ points. Hence, we expect a significant difference in health status of 0.5 points in patients using the portal (2.0-1.5 = 0.5 points). To measure significant differences in health status (>0.5 CCQ points) at 80 % power, SD 0.75 and *α* = 0.05, 37 patients must be included. Based on an estimated 20 % drop-out during the study, 45 (37/0.80) patients are needed. As we use two different organisational implementation methods within two of the care groups 2*45 = 90 patients must be included in those settings. In the third care group only one organisational implementation method (free use) is used. Hence, a total of 225 (90 + 90 + 45) patients are necessary to achieve sufficient statistical power.

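### The group 1 time series can estimate only the combined effect of a new disease management programme and the portal, although the plan labels it the effect of the portal.

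*Protocol article*

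**What the plan says.** **Timing.** The text after Fig. 3 (Methods/Design) says "Group 1 will start with COPD disease management simultaneous to implementation of the web portal". By contrast, "Group 2 is used to working with a COPD disease management program", and group 3 is described in the same way.

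**Content.** The Intervention section (text after Fig. 5) describes what is new in group 1. GPs and practice nurses are trained in COPD disease management, and then "they implement the COPD care program in their practices under supervision of a specialized nurse". A research nurse helps practice nurses bring their records up to date. Group 2 caregivers receive a short training in a programme they already use, plus training in the portal. Group 3 caregivers receive none.

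**Analysis.** Methods/Design states: "We chose for an interrupted time series (ITS) design to evaluate clinical outcomes (CCQ) within each group". The reason given is that the care groups differ, so "we can not compare the COPD cohorts by combining data across three different groups".

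**Label.** The text after Fig. 3 says: "The clinical effects of the web portal will be investigated using an interrupted times series (ITS) study design". Data analysis repeats it: "To investigate the effect of the use of the web portal on the primary clinical outcomes, the ITS data will be analysed". Neither place treats group 1 differently.

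**Power premise.** The Power calculation section says: "In our study we offer patients a web portal in addition to their regular disease management program".

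**The concern.** An ITS separates the intervention effect from a trend that was already under way. It cannot separate two interventions that begin at the same interruption. In group 1 the second intervention is substantial: a care programme, staff training and supervised roll-out in the practices. The article itself expects the quality of care organisation to matter, since the Discussion hypothesises higher portal use and therefore better health status in well-organised care groups with skilled staff.

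The primary aim is the effect of the portal on clinical outcomes. If the group 1 series is reported under the label the article gives it, an improvement in the Clinical COPD Questionnaire (CCQ) could be attributed to the portal when the programme produced some or all of it. The Discussion claims control of organisational confounding. Its limitations mention other projects in the care groups but not this co-intervention, which is part of the design.

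**Working it through.** **1. The plan's own figures.** Inputs from the Power calculation section: difference 0.5 CCQ points, SD 0.75, power 80%, α = 0.05 (two-sided assumed).

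- Normal approximation: n = 2 × [0.75 × (1.96 + 0.842) / 0.5]² = 35.3, so 36. The two-sample t version gives 36.3, so 37. The stated 37 is reproduced.
- The stated 45 per cell equals 36/0.80. Taken literally, 37/0.80 = 46.25. This is a rounding matter unrelated to the present point.
- Total: 90 + 90 + 45 = 225. Group 1 share: 90/225 = 40%.

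**2. What the group 1 series can identify.** The CCQ is taken three times at each of four measurements, giving 12 occasions. A standard segmented regression is

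Y(t) = b0 + b1·t + b2·S(t) + b3·S(t)·(t − t0) + error,

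where S(t) is 0 before the portal starts at t0 and 1 afterwards. The terms b2 and b3 are the step and slope change for the portal. If the programme starts at the same t0, its step and slope terms use the same two columns.

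| Model | Columns | Rank |
|---|---|---|
| Intercept, trend, portal step, portal slope | 4 | 4 |
| The same plus programme step and slope | 6 | 4 |

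The result is the same whether 3 or 6 of the 12 occasions precede the interruption. Only the sums (portal step + programme step) and (portal slope + programme slope) can be estimated. More patients do not change this.

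**3. Whether another contrast within the design rescues it.**

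- A control series from another group: the ITS is run within each group, and the article rules out combining the groups.
- The randomisation in group 1: 1a and 1b differ in support for using the portal. Both have the programme and both have the portal, so there is no arm without one of them.

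**4. Illustration of possible size.** The article gives no programme effect, so a range is assumed. The true portal effect is set to 0. The contrast is the two-sample one behind the sample size, not the planned ITS. Standard error = 0.75 × √(2/m), with m = 37 (0.174) or m = 90 × 0.80 = 72 (0.125). The chance of a significant result that would be labelled a portal effect is:

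| Assumed programme effect (CCQ points) | m = 37 | m = 72 |
|---|---|---|
| 0 | 5% | 5% |
| 0.1 | 9% | 13% |
| 0.2 | 21% | 36% |
| 0.3 | 40% | 67% |
| 0.4 | 63% | 89% |
| 0.5 | 82% | 98% |

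These figures show the direction and sensitivity of the problem. They do not estimate the bias.

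**The case against.** **The package is disclosed.** The Intervention section lists training and programme implementation among the actions of the intervention. Methods/Design says that eHealth is not an isolated clinical intervention and presents an implementation study. A programme-plus-portal reading of group 1 is therefore available to a careful reader. That is fair, but the primary aim, the ITS description, the analysis text and the power premise all name the portal, and none makes an exception for group 1.

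**The steps may not coincide exactly.** The Intervention section orders them: training, then programme implementation, then the offer of the portal. The figures that might show exact timing are not available here. However, the text after Fig. 3 calls the two starts simultaneous, and no measurement phase between them is described.

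**Group 1 is not uninformative.** A reader might infer that these patients say nothing about the portal apart from the programme. That goes too far. The randomised 1a versus 1b comparison varies support for portal use while holding the programme constant, and portal use is logged continuously. This gives some evidence on portal use, though not an estimate of the effect of having the portal.

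**No planned estimate loses patients.** A reader might subtract 90 from 225 and treat the remainder as the sample left for the portal effect. The article does not support this. The ITS is not pooled across groups, each implementation cell is sized separately, and the group 2 and group 3 series keep all their patients.

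**Conclusion.** The point holds for group 1. Its ITS is valid for programme plus portal, but it supports no conclusion about the portal alone, and the power premise does not describe this group. It concerns 90 of 225 planned patients, 40% of enrolment. The bias in a portal-only reading is the programme's own effect, whose size is unknown.

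The conclusion rests on the stated simultaneous start and on group 1 having had no such programme before. The latter is inferred from the wording that it will start one, set against the two groups already used to working with one.

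Two stronger readings should be avoided. First, a reader might take groups 2 and 3 as equally clean. They are not: group 2 receives short caregiver training with the portal, so only group 3 has no described co-intervention, and the article says group 3 uses a less advanced portal. Second, a reader might conclude that a group 1 improvement will certainly be misattributed. The article leaves the final ITS method open and fixes no rule for the group 1 conclusion. The fault lies in the label and the premise.

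**What to change.** 1. In Methods/Design and Data analysis, state that the group 1 ITS estimates the combined effect of the new programme and the portal, and supports no portal-only conclusion.
2. Rest the portal claim on the group 2 and group 3 series, analysed separately. Add the caveat that group 2 caregivers are trained at portal start, so only group 3 has no described co-intervention.
3. Reconcile the Power calculation premise with the description of group 1 after Fig. 3.
4. Name the co-intervention among the limitations in the Discussion.
5. Keep group 1 for the randomised 1a versus 1b support comparison, which is unaffected because both arms receive programme and portal.

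The cost is rewording only, with no change to recruitment, measurements or the other two series. The downside is that the portal-only claim no longer has support from group 1.
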